### Data collection and quality assurance

All staff involved in the conduct of trial is certified in Good Clinical Practice. Two dedicated research supervisors are involved with day-to-day monitoring, ensuring quality and adherence to protocols at each step of data collection from enrollment to follow up. Refresher trainings are conducted for all staff on a quarterly basis to ensure uniformity in assessment and data collection.

Detailed case report forms (CRFs) are used for recording information on eligibility, randomization, demographics, air quality, clinical history, vital status, follow-up, adverse event, protocol violation, protocol deviation, TF and relapse. Alongside documenting clinical information, video recording of child symptoms and nasopharyngeal swab collection is done after the caregiver has provided oral consent. Nasopharyngeal swabs are collected using WHO recommendations. IMCI treatment algorithms are followed for treatment of children. Blood cultures are collected for children with TF or relapse. All TFs are assessed by physician and managed in accordance with the WHO handbook of caring for sick child [29]. Case summaries are made for all participant assessed for eligibility and are discussed within the research team for quality. 10 % of the enrollments are also concurrently re-assessed by the research supervisor for quality assurance.

### Data management

At the field sites, all CRFs are checked for errors, consistency, missing or illogical values. After the initial quality check, these case files are sent to the study data management unit for data entry. Logs of CRF transfers and handling are maintained for the custody chain. All data is doubled entered using a customized SQL-based relational database management system with an audit trail. Data is assessed for logical and consistency checks on a weekly basis. Discordant entries are verified against the original CRFs. After entry, the physical forms are stored in a secured location at the data management unit. Access to data is restrictive as to maximize security and confidentiality.

### Outcomes

The primary outcome will be cumulative treatment failure at or before day 3 (Table 3). Secondary outcome includes treatment adherence, new onset infectious co-morbidity, severe and non-severe adverse event, relapse, pneumococcal and viral carriage and cost of treatment.

**Table 3 Tab3:** Treatment failure criteria^a^

Criterion	Days of assessment						
	0	1	2	3	5	14	21
Death	Treatment failure				Relapse		Vital status check
Any danger sign^b^							
Onset of lower chest in drawing							
Hospitalization due to any reason							
Change of antibiotic by study physician for new onset comorbidity or serious non-fatal antibiotic associated adverse event							

^a^Chest X-ray, blood for culture is processed for all treatment failures and relapses

^b^Unconscious/lethargy, convulsions, unable to feed, stridor when calm, hypoxia (paO2 < 90 %) in air, vomits everything

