**Methods/design:**

This is a randomized double blinded placebo-controlled non-inferiority trial using parallel assignment with 1:1 allocation ratio, to be conducted in low income squatter settlements of urban Karachi, Pakistan. Children 2–59 months old with fast breathing, without any WHO-defined danger signs and seeking care at the primary health care center are randomized to receive either three days of placebo or amoxicillin. From prior studies, a sample size of 2430 children is required over a period of 28 months. Primary outcome is the difference in cumulative treatment failure between the two groups, defined as a new clinical sign based on preset definitions indicating illness progression or mortality and confirmed by two independent primary health care physicians on day 0, 1, 2 or 3 of therapy. Secondary outcomes include relapse measured between days 5–14. Modified per protocol analysis comparing hazards of treatment failure with 95 % confidence intervals in the placebo arm with hazards in the amoxicillin arm will be done.

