The last comprehensive Cochrane review looking at use of antibiotics in pneumonia conducted up to 2009 showed that among 27 studies, comparing multiple antibiotics, none were found to compare antibiotic with placebo [23]. Another Cochrane review done last year which looked at antibiotic versus no antibiotic therapy in children with non-severe pneumonia and wheeze did not find a single study meeting inclusion criteria and concluded that there is a lack of evidence and randomized controlled trials are needed to address this question in representative population [24]. Two recent randomized controlled trials (RCTs) compared placebo to amoxicillin for the management of non-severe pneumonia, now called fast breathing pneumonia. Hazir et al [5] conducted a double-blinded, RCT of oral amoxicillin versus placebo for non-severe pneumonia in four centers in Pakistan, using age-dependent WHO cut-offs for dosing. Cumulative treatment failure (TF) by day 3, defined as appearance of any danger sign or onset of lower chest indrawing, was similar in both groups: 7.2 % (31/431) of children in the amoxicillin group and 8.3 % (37/442) in the placebo group. Between the arms there was no statistically significant difference in relapse by day 14, the number of children requiring change (or initiation) of antibiotics, the number of children who developed danger signs, or the number of children requiring hospitalization. There were no deaths. The second randomized placebo controlled multi-centre trial was conducted in India in out-patient clinics associated with tertiary care hospitals [4]. This trial used the WHO criteria for non-severe pneumonia, but only enrolled children with wheeze (audible or auscultatory). TF rates at day 4 was defined as development of WHO-defined severe or very severe pneumonia, hypoxaemia (SpO_2_ < 90 %), fever (temperature >101^0^ F) or persistence of non-severe pneumonia, or wheeze. TF among placebo recipients was 24.0 % (201/836), while among the amoxicillin group it was 19.9 % (166/835). The rate difference was 4.2 % (95 % CI 0.2 to 8.2); however, there was no difference in the rates of relapse. Clinical failure due to the development of severe or very severe pneumonia or hypoxemia was similar between groups. These trials were conducted before Hib and pneumococcal vaccines were introduced in the local setting.

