### Recruitment and follow-up

Children between 2 to 59 months old with cough or difficult breathing, presenting at the participating PHCs are screened for eligibility by the study physicians. If eligible the parent/guardian is referred to an independent physician to obtain written informed consent. If consent is given and child is enrolled then randomization serial identification number will be assigned. All enrolled children will receive study drug by CHW in accordance with the randomization number in morning and evening on day 0, 1 and 2.

Children are followed for compliance and outcome twice daily on days 0, 1, 2, 3, with a morning assessment by a study physician in the study clinic and a home visit in the evening by a CHW. Subsequently, children are seen by a study physician once on days 5, 14 and 21. At follow-up visits participants will be examined by study physician in the morning and CHW in the evening for resolution of high respiratory rate along with signs of treatment failure and relapse (Fig. 2). All adverse events are recorded on the adverse event reporting form (AERF). The schedule of follow-up is derived from our experience of a trial in younger infants [27] and taking into consideration safety of the enrolled children.

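### An antibiotic given by day 3 for unresolved fast breathing alone is never a Table 3 failure, and no stated analysis shows what that does to the comparison

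*Protocol article*

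**What the plan says.** The Outcomes section fixes the endpoint: "The primary outcome will be cumulative treatment failure at or before day 3". Table 3 then lists five criteria. Besides death and any danger sign, they are "Onset of lower chest in drawing", "Hospitalization due to any reason" and "Change of antibiotic by study physician for new onset comorbidity or serious non-fatal antibiotic associated adverse event". The abstract describes failure in the same spirit, "defined as a new clinical sign based on preset definitions indicating illness progression or mortality".

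Persistence is observed. Under Recruitment and follow-up, the plan for each child reads "examined by study physician in the morning and CHW in the evening for resolution of high respiratory rate along with signs of treatment failure and" (the sentence ends by naming relapse as well). Non-resolution nevertheless appears neither in Table 3 nor among the secondary outcomes named in the Outcomes section.

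On treatment during the trial, Data collection and quality assurance says "IMCI treatment algorithms are followed for treatment of children". The article has no explicit rule on antibiotics for a child who is not improving but has no failure sign. The non-compliance paragraph under Limitations and bias says that families are asked daily about antibiotics from outside, and expects 3% of children to seek therapy elsewhere.

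Under Statistical analysis, the primary analysis is modified per protocol: at least 5 of 6 doses, with 4 in the first two days. Intention to treat is done for comparison.

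**The concern.** A blinded physician's antibiotic decision is accepted as failure for two reasons, a new comorbidity and a serious antibiotic adverse event. The reason closest to the research question, that the index illness has not resolved, is not among them. An antibiotic for a new comorbidity counts; an antibiotic for the pneumonia that brought the child into the trial does not.

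The omission need not be neutral between arms. If amoxicillin works at all, starts for non-improvement should be commoner on placebo, while an antibiotic adverse event fits mainly the amoxicillin arm. Both tendencies push the measured difference towards non-inferiority, which is the result that the Conclusion section says may make the case for changing guidelines. Early rescue may also prevent the danger sign that would have counted. Intention to treat uses the same endpoint, so it does not expose the problem.

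**Working it through.** **1. The plan's own figure.** Inputs from the Sample size section: failure 5% in both arms, one-sided alpha 0.05, power 85%, margin 2.5 points, 10% lost or not per protocol.

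n per arm = (1.645 + 1.036)² × 2 × 0.05 × 0.95 / 0.025² = 1092.8, so 1093. Then 1093 / 0.90 = 1214.4, so 1215 per arm and 2430 in total. The stated size reproduces and is not in question here.

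**2. How the child is classified.** Take a child with persistent fast breathing, no danger sign, no indrawing and no admission, who is given a non-study antibiotic by day 3. Study doses are due morning and evening on days 0, 1 and 2, so the fifth dose is the morning dose of day 2.

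| Course | Modified per protocol | Intention to treat |
|---|---|---|
| Antibiotic started, at least 5 study doses taken (4 in the first two days) | Non-failure | Non-failure |
| Antibiotic started and study drug stopped before the fifth dose | Excluded | Non-failure |
| Later danger sign, indrawing or admission by day 3 | Failure if the dose rule is met | Failure |

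In the first two rows the event is not counted in either population.

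**3. Illustration of size.** The documents give no rate for these starts, so the following is assumed: failure including them is 7.5% on placebo and 5.0% on amoxicillin (exactly at the margin), with 1093 evaluable per arm and all children kept in the analysis. Let e be the excess of uncounted starts on placebo. The measured placebo rate is p = 0.075 − e and the measured difference is d = p − 0.05.

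SE = √[p(1 − p)/1093 + 0.05 × 0.95/1093]; P(declare non-inferior) = Φ[(0.025 − d)/SE − z].

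| e (points) | d (points) | SE | (0.025 − d)/SE | P, z = 1.645 | P, z = 1.96 |
|---|---|---|---|---|---|
| 0 | 2.5 | 0.01034 | 0 | 0.050 | 0.025 |
| 0.5 | 2.0 | 0.01015 | 0.493 | 0.125 | 0.071 |
| 1.0 | 1.5 | 0.00995 | 1.005 | 0.261 | 0.170 |
| 1.5 | 1.0 | 0.00975 | 1.538 | 0.458 | 0.337 |

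Both z values are shown because the Sample size section plans at one-sided 0.05 but judges by a 95% interval.

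The same formula can be read from the other side. With listed failures at 5% in each arm, the chance of declaring non-inferiority is 0.85 whatever the number of uncounted starts. If starts were counted, and occurred only on placebo at 1, 2 or 2.5 points, it would be 0.46, 0.125 or 0.05.

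**4. Cost of widening the primary endpoint instead.** At 6% in both arms, n = (1.645 + 1.036)² × 2 × 0.06 × 0.94 / 0.025², so 1298 per arm, and 2596 / 0.90 gives about 2885 children. At 7% the total is about 3329. With 1093 evaluable per arm, power at 6% falls to about 0.79.

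**The case against.** The strongest reply is that the endpoint is a deliberate choice. The abstract asks for a new sign of progression, and leaving out mere persistence fits that. The Background describes a close precedent: the earlier placebo trial in Pakistan defined failure by day 3 as a danger sign or chest indrawing, reported antibiotic change or initiation separately, and found no significant difference in it. This stands as a reason not to call the primary endpoint wrong. With 873 children (431 + 442), that result does not exclude a small excess. That trial also did compare antibiotic change or initiation between arms, which the secondary outcomes named here do not.

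A reader might infer that every such child is scored as a success in the primary analysis. That is too strong: a child taken off study drug before the fifth dose is excluded. Exclusion also hides the event, but by a different route. Nor are children who worsen missed as a group, since a danger sign, indrawing or any admission counts.

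A reader might also infer that the protocol provides for rescue antibiotics for non-improvement. It does not say so. The possibility is inferred from the reference to IMCI algorithms and from outside therapy.

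The Indian trial in the Background may look like proof, because its broad failure rate differed by 201/836 − 166/835 = 4.2 points while "Clinical failure due to the development of severe or very severe pneumonia or hypoxemia was similar between groups". But it enrolled only children with wheeze, and its composite also included fever and persistent wheeze. The gap cannot be credited to persistent pneumonia, still less to antibiotic starts. It shows only that the choice of definition can matter on the scale of a 2.5-point margin.

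Finally, the error rates above redefine failure more broadly than the endpoint for which the margin was set. For the protocol's own endpoint, this mechanism does not inflate type I error. That is correct, and the figures should be read as an illustration.

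**Conclusion.** The point holds as a gap in outcome scoring. An antibiotic for unresolved fast breathing by day 3 is never a failure: it is a non-failure in intention to treat, and a non-failure or an exclusion in the modified per protocol set. If such starts are commoner on placebo, the bias runs towards non-inferiority, and the stated intention-to-treat comparison would not reveal it.

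The size is unknown. The range of about 12% to 46% instead of 5% (7% to 34% instead of 2.5% at z = 1.96) rests on assumed placebo excesses of 0.5 to 1.5 points and on a broader failure rate exactly at the margin. The documents do not support saying that the primary endpoint is invalid or that such starts will be frequent. They do support saying that a non-inferiority result would be open to this challenge, and that data the trial already plans to collect could answer most of it.

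**What to change.** Keep the Table 3 primary endpoint and add two items.

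- **Sensitivity analysis**, in both the modified per protocol and intention-to-treat populations: score as treatment failure any non-study antibiotic started or changed by day 3 for persistent or worsening respiratory illness, and do not exclude such children for missed study doses.
- **Secondary outcome**: fast breathing still above the age-specific entry cut-off at the day 3 visit, reported as a between-arm difference with a confidence interval, from the respiratory rates already taken.

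The cost is one reason field on the form and slightly more analysis, with no new visit or test. The power of the primary analysis is unchanged. The sensitivity analysis itself has less power if the added events are common, so it supports the primary result and should not replace it. Moving these events into the primary endpoint is the alternative, but it would raise the failure rate and take power below the stated 85% at 2430 children.

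Both items concern how outcomes are scored and reported. Neither sets a rule for when a child should be treated.

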### Statistical analysis

Baseline characteristics will be compared by analyzing differences in means and proportions among the study arms using the *chi-square* test for proportions and Student’s *t*-test for continuous variables. The primary analysis of outcomes will be a modified per protocol analysis comparing hazards of treatment failure with 95 % confidence intervals in the placebo arm with hazards in the amoxicillin arm. In order for an enrolled child to be included in the modified per protocol analysis, s/he must have received 5 out of 6 doses, including 4 doses in the first two days. Adjusted hazard rate ratios will be estimated accounting for the effect of any baseline variable found to differ between the two arms. Intention to treat analysis will also be performed for comparison.

Additionally, analyses will be done to identify predictors of treatment failure. Baseline characteristics between cumulative treatment success and failure groups by day 3 will be compared using the *chi square* test for categorical variables and Student’s *t*-test for continuous variables. A multivariate model will be constructed to look for determinants of cumulative treatment failure at day 3. All analysis will be done using STATA version 12. Sub-group analyses will be performed by age category, nasopharyngeal carriage, wheezing and initial fever.

Investigators propose to conduct one interim analysis using the O’Brien Fleming rule when 50 % per protocol subject accrual has been achieved. Termination will be done if p < 0.01 is observed with respect to the null hypothesis of inferiority. Final analysis will be done once enrollment is complete.

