### Hypothesis

The null hypothesis for this trial is that the absolute treatment failure rate of children 2–59 months of age presenting at a primary healthcare (PHC) facility for treatment of WHO defined fast breathing pneumonia who receive 3 days of placebo is worse than 3 days of amoxicillin by 2.5 % (TF_placebo_—TF_amoxicillin_ > 2.5 %, assuming TF of 5 % in amoxicillin group).

The alternate hypothesis is that absolute treatment failure rate of children 2–59 months of age presenting at a primary healthcare (PHC) facility for treatment of WHO defined fast breathing pneumonia who receive 3 days of placebo is equal to or not worse than 3 days of amoxicillin by 2.5 % (TF_placebo_—TF_amoxicillin_ ≤ 2.5 % assuming TF of 5 % in amoxicillin group).

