### Sample size

In the study of Hazir et al [28], cumulative TF rates at day 3 were reported to be between 4 % and 7 % in tertiary level hospital setting. Given that the currently described study is conducted in a primary care setting, investigators have estimated that the TF rate of 5 %. Assuming a TF rate of 5 % in both the arms, using one sided alpha of 0.05, power of 85 %, non-inferiority margin of 2.5 % and an expected 10 % lost to follow-up/non per protocol, the minimum total estimated sample size required is 2430. Placebo will be judged to be “no worse” than amoxicillin if the lower bound of the 95 % confidence interval lies in the allowed margin.

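### The primary analysis compares hazards of treatment failure, but the hypotheses, the 2.5-point margin and the sample size concern the absolute difference in cumulative failure by day 3, and nothing in the protocol links the two scales

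*Protocol article*

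**What the plan says.** The design is set on the absolute scale in four places of the protocol article:

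- **Hypothesis:** "The null hypothesis for this trial is that the absolute treatment failure rate of children" given placebo exceeds that on amoxicillin by 2.5%. It is written as placebo minus amoxicillin, with 5% failure assumed on amoxicillin.
- **Abstract, Methods/design:** "Primary outcome is the difference in cumulative treatment failure between the two groups".
- **Outcomes:** "The primary outcome will be cumulative treatment failure at or before day 3".
- **Sample size:** "Assuming a TF rate of 5 % in both the arms", "using one sided alpha of 0.05", 85% power and a "non-inferiority margin of 2.5"%. Non-inferiority is then judged from a 95% confidence interval, without saying of which measure.

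The analysis is set on another scale. Under Statistical analysis: "The primary analysis of outcomes will be a modified per protocol analysis comparing hazards of treatment failure with" 95% confidence intervals, placebo against amoxicillin. The abstract repeats this. The same section continues: "Adjusted hazard rate ratios will be estimated", accounting for baseline variables that differ between the arms. The article states no hazard-ratio margin, no conversion of the 2.5 points to the hazard scale, and no analysis of the difference in cumulative failure.

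**The concern.** A non-inferiority conclusion comes from setting a confidence limit against a margin on the same scale. Here the only interval attached to the primary analysis is for a comparison of hazards, while the only margin is a difference between two proportions. This is not an estimator detail that an article can leave to the analysis plan: the article states both scales, and they differ.

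The choice of scale can decide the result. A fixed difference and a fixed ratio agree at only one control-arm rate. If the scale, or the rate used for conversion, is settled after unblinding, that choice could determine whether placebo is called non-inferior. The Conclusion section says such a finding may make the case for changing treatment guidelines.

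**Working it through.** **Inputs.** From Sample size: failure 5% in both arms, margin 0.025, one-sided alpha 0.05, power 85%, 10% loss or non-per-protocol, and a cited range of 4% to 7% for day-3 failure. From Design: 1:1 allocation. The hazard-ratio steps assume proportional hazards.

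**1. Reproduce the sample size on the difference scale.**
n per arm = (z₀.₉₅ + z₀.₈₅)² × [p(1−p) + p(1−p)] / margin²
= (1.645 + 1.036)² × (2 × 0.05 × 0.95) / 0.025²
= 7.189 × 0.095 / 0.000625 = 1092.8, so 1093 per arm and 2186 in total.
Allowing for 10% loss: 1093 / 0.90 = 1214.4, so 1215 per arm and **2430** in total. This matches the stated figure exactly, so the trial was sized for an absolute difference.

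**2. Convert the margin to a hazard ratio.**
HR = ln(1 − p − 0.025) / ln(1 − p), where p is the amoxicillin failure rate.

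| Amoxicillin failure | HR equal to +2.5 points | Points allowed by a fixed HR of 1.52 |
|---|---|---|
| 4% | 1.65 | 2.0 |
| 5% | 0.0780 / 0.0513 = 1.52 | 2.5 |
| 7% | 1.38 | 3.4 |

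The last column is 1 − (1 − p)^1.52 − p.

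**3. Can the two scales disagree?** Take 1093 per arm, a two-sided 95% interval, and a hazard-ratio margin of 1.52 converted at the planning rate. The counts are illustrative. The hazard ratio is approximated from the proportions, with SE(log HR) = √(1/x₁ + 1/x₀), where x₁ and x₀ are the failure counts on placebo and amoxicillin.

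- *33 amoxicillin and 38 placebo failures (3.0% and 3.5%).* Difference 0.46 points, SE 0.76, upper limit 0.46 + 1.96 × 0.76 = 1.9 points: inside 2.5. HR 1.15, SE(log) 0.238, upper limit 1.84: outside 1.52.
- *80 amoxicillin and 88 placebo failures (7.3% and 8.1%).* Difference 0.73 points, SE 1.14, upper limit 0.73 + 1.96 × 1.14 = 3.0 points: outside 2.5. HR 1.10, SE(log) 0.154, upper limit 1.49: inside 1.52. With a 90% interval the limits are 2.6 points and 1.42, so the conflict remains.

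The second case is the more serious one: the hazard scale passes placebo while the stated absolute limit is exceeded.

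**4. Power if 1.52 were the margin and the true HR were 1.**
Expected failures = 0.05 × 2186 = 109.3. SE(log HR) = 2 / √109.3 = 0.191. ln 1.52 = 0.419, and 0.419 / 0.191 = 2.19.
Power at one-sided 0.05 = Φ(2.19 − 1.645) = **71%**.
On the difference scale, SE = √(0.095 / 1093) = 0.00932, and Φ(0.025 / 0.00932 − 1.645) = **85%**.
Reaching 85% on the hazard scale would take 4 × 7.189 / 0.419² ≈ 164 failures, or 165 with the Schoenfeld formula before rounding of inputs (169 with Freedman's).

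**The case against.** The best defence is that, read together, the sections intend a decision on the difference scale. The abstract defines the primary outcome as a difference, the Hypothesis section fixes the margin on it, and the Sample size section supplies an interval-against-margin rule. Day-3 cumulative failure in each arm can also be derived from the same time-to-event data. All of that stands. It shows that the repair is easy and probably matches the intention. It does not remove the contradiction, because the analysis named as primary is still the hazard comparison.

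Four stronger readings are tempting but not supported:

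- *The margin could be converted only once the trial's own rates are known.* The Hypothesis section ties the margin to 5% failure on amoxicillin, so 1.52 can be derived beforehand. What is true is that no hazard-ratio margin is stated, and that a fixed one drifts from 2.5 points if the control rate is not 5%.
- *The primary analysis is literally a hazard ratio.* The word ratios is attached only to the adjusted estimates. A ratio is the natural reading of the unadjusted comparison, but an inference. A difference in cumulative hazards would be numerically close here (0.0780 − 0.0513 = 0.027 against 0.025), yet it is still not the stated quantity.
- *Power falls from 85% to 59%.* The 59% uses a two-sided 95% interval and the 85% uses one-sided 0.05, which brings in a separate mismatch between alpha and interval. Like for like, it is 71% against 85%, or 59% against 76%.
- *A non-significant hazard ratio would be taken as non-inferiority.* The protocol nowhere proposes this; it sets an interval against a margin.

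**Conclusion.** The point holds as an internal contradiction: the named primary analysis does not directly test the stated hypothesis, and the protocol supplies no link between them. It should be corrected before unblinding, because the choice of scale can reverse the conclusion.

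Over the cited 4% to 7% range, the hazard ratio equal to 2.5 points runs from about 1.65 to 1.38, and is 1.52 at the planning rate. Using 1.52 as the margin would leave about 71% power at one-sided 0.05 rather than 85%. These figures assume proportional hazards, about 109 failures among 2186 evaluable children, no true difference between the arms, and a margin of 1.52 that the protocol itself never adopts.

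A reader might infer that the sample size is wrong. It is not: 2430 is exactly right for the difference scale.

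**What to change.** In Statistical analysis, and in the matching sentence of the abstract, name the difference in cumulative treatment failure by day 3 (placebo minus amoxicillin) as the primary analysis. State that its confidence interval is compared with +2.5 percentage points. Stratifying the estimate by the randomised age group is preferable, since allocation was stratified that way, but the correction does not depend on it. Keep hazard ratios, unadjusted and adjusted, as supportive analyses.

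If the investigators prefer hazards as primary, they would instead need to state a hazard-ratio margin in advance, justify it against the 2.5 points, and accept or address the lower power shown above.

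The recommended change costs only wording. It needs no new data, and the sample size stays at 2430.

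### The five-dose rule for the primary per-protocol set can remove treatment failures that occur before day 2, and no exception is stated for them

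*Protocol article*

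**What the plan says.** All references are to the protocol article.

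- **Primary set** (Statistical analysis): "The primary analysis of outcomes will be a modified per protocol analysis comparing hazards of treatment failure". To be included, "s/he must have received 5 out of 6 doses, including 4 doses in the first two days". The dose rule is the only explanation given of the word modified.
- **Dosing** (Recruitment and follow-up): study drug is given "in morning and evening on day 0, 1 and 2", six doses in all.
- **Endpoint** (Outcomes): "The primary outcome will be cumulative treatment failure at or before day 3". The abstract likewise has failure "confirmed by two independent primary health care physicians on day 0, 1, 2 or 3 of therapy". Table 3 lists the criteria: death, any danger sign, new lower chest indrawing, "Hospitalization due to any reason", and a change of antibiotic by the study physician for a new comorbidity or a serious antibiotic-related adverse event.
- **Intention to treat** (Statistical analysis): "Intention to treat analysis will also be performed for comparison".
- **Margin** (Hypothesis; Sample size): 2.5 percentage points on the absolute difference in failure rates, assuming 5% failure on amoxicillin.

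**The concern.** Entry to the primary set depends on something that happens after randomisation and that the endpoint itself can prevent. A child who fails on day 0 or day 1 and takes no further study drug cannot reach five doses. That child has met the primary outcome and is then dropped from the analysis of it. The events at risk of removal are the earliest ones, and they include any early death.

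If placebo is worse, it has more failures to lose. Removing a share of failures from both arms pulls the absolute difference towards zero, which is the favourable direction in a non-inferiority trial. The question answered also shifts, from cumulative failure by day 3 towards failure among children who stayed well enough to complete five doses. The intention-to-treat analysis would show the missing events, but it is given no part in the decision. The Conclusion says the result may support a change in treatment guidelines, so a false claim of non-inferiority would matter.

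**Working it through.** **Step 1. Timing.** Two doses a day from day 0 put doses 1–2 on day 0, doses 3–4 on day 1 and doses 5–6 on day 2. The endpoint window is day 0 to day 3. Failures on days 0 and 1, and any on day 2 before dose 5, are therefore endpoint events in children who have not yet had five doses.

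**Step 2. Who is excluded.** For death before dose 5, exclusion is certain. For hospitalisation, change of antibiotic, inability to feed or vomiting everything, it is the natural reading but an inference, because the article does not say that study drug stops at failure. No sentence exempts children who fail first.

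**Step 3. The plan's own sample size.** Inputs from Sample size: 5% failure in both arms, margin 0.025, one-sided alpha 0.05, power 85%, 10% loss or non per protocol.

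n per arm = (1.645 + 1.036)² × 2 × 0.05 × 0.95 / 0.025² = 7.189 × 0.095 / 0.000625 = 1092.8, so 1093.

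1093 / 0.90 = 1214.4, so 1215 per arm and 2430 in total. The stated figure reproduces.

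**Step 4. Effect of the rule at the null boundary.** Take 1093 evaluable children per arm before the removal, and true failure of 7.5% on placebo and 5% on amoxicillin (about 82 and 55 expected failures). Let f be the share of failures that precede dose 5 and are excluded. The article does not give f, so it is an assumption, here equal in both arms.

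- Observed rate in an arm: q = p(1 − f) / (1 − pf), from n(1 − pf) children.
- SE = √[q_P(1 − q_P)/n_P + q_A(1 − q_A)/n_A], unpooled.
- Chance of declaring non-inferiority = Φ[(0.025 − (q_P − q_A))/SE − 1.645].

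Worked for f = 50%: q_P = 0.0375/0.9625 = 0.0390 and q_A = 0.025/0.975 = 0.0256, a difference of 0.0133. SE = 0.00768. (0.025 − 0.0133)/0.00768 = 1.52, and Φ(1.52 − 1.645) = 0.45.

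| f (assumed) | Placebo | Amoxicillin | Difference (points) | False non-inferiority |
|---|---|---|---|---|
| 0 | 7.5% | 5.0% | 2.5 | 5% |
| 10% | 6.8% | 4.5% | 2.3 | 8% |
| 25% | 5.7% | 3.8% | 1.9 | 15% |
| 50% | 3.9% | 2.6% | 1.3 | 45% |
| 67% | 2.6% | 1.7% | 0.9 | 81% |

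A simulation of 200,000 trials per row gave 5%, 16%, 46% and 80% for f of 0, 25%, 50% and 66.7%.

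**Step 5. What the direction depends on.**

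- *Unequal early shares, same true rates.* With 60% on placebo and 40% on amoxicillin, the difference falls to 0.1 point and false non-inferiority is 94%. With 40% and 60%, the difference is 2.6 points and false non-inferiority is 4%, so the distortion disappears.
- *Equal true rates (5% each) and equal f.* The difference is unbiased, but fewer events make passing easier: the chance of declaring non-inferiority rises from 85% to 98% at f = 50%.
- *Ratio scale.* With equal f the risk ratio hardly moves: 1.50 at f = 0 and 1.52 at f = 50%.
- *Choice of bound.* Sample size also mentions a 95% confidence interval. With 1.96 in place of 1.645, the baseline is 2.5%, and f of 25% and 50% give 9% and 33%. The pattern is the same.

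**The case against.** **Exclusion is certain only for death.** The protocol expects deaths to be very rare (Possible risks), says that all enrolled children receive study drug on days 0 to 2, and sends failures to management under a WHO handbook that is not shown. A child who fails and still takes five doses stays in the set. This stands: it makes the excluded share smaller and unknown, but does not make it zero.

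**The direction is not fixed.** Table 3 counts an antibiotic change for a serious antibiotic-related adverse event as failure. Such events should fall mainly on amoxicillin, and removing them would work against placebo. A reader might infer that the rule always favours non-inferiority. The document does not support that, as Step 5 shows.

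**The primary comparison is stated in hazards,** and a ratio is nearly immune when early shares are equal. This is correct, but the only margin in the document is absolute.

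**Per-protocol primary with intention to treat alongside is a common non-inferiority layout,** and the article is a condensed one, so the full protocol may elaborate on the word modified. Both are fair. Even so, the inclusion rule is printed in explicit terms without an exception, so this is a stated rule and not a detail left out.

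**Conclusion.** The point holds in a limited form. The dose rule, the dosing schedule and the endpoint window do not fit together: as written, a child who dies before the fifth dose, and probably one hospitalised or switched to another antibiotic before it, is an endpoint event outside the primary analysis. On the absolute 2.5-point scale this favours non-inferiority when placebo is truly worse and early failure is not clearly commoner on amoxicillin. The first of these conditions is the case that a non-inferiority test has to guard against.

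The size rests on the early share, which is assumed. Even 10% lifts the false-claim rate from 5% to about 8%, and 50% lifts it to about 45%. These figures illustrate the risk and do not forecast it. It would go too far to say that every early failure is excluded, or that the bias must run one way.

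**What to change.** Change the inclusion sentence so that adherence is judged for every child, whether or not the child fails, only on doses due before treatment failure or censoring. One example is at most one due dose missed overall, and none missed among those due in the first two days. A child who was adherent up to failure then stays in the primary set and counts as an event. With no early failures removed (f = 0), the false-claim rate returns to the nominal 5%.

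The same rule must apply to failures and non-failures. Keeping all failures whatever their adherence would itself select on outcome. With 5% non-adherence unrelated to outcome, 5.0% becomes 0.05/(0.05 + 0.95 × 0.95) = 5.2% and 7.5% becomes 0.075/(0.075 + 0.925 × 0.95) = 7.9%, a difference of 2.6 points.

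Report the intention-to-treat result against the same 2.5-point margin, and require it to be consistent before non-inferiority is claimed.

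Cost: one changed sentence on the analysis set, a statement of the role of intention to treat, and one programmed flag. The sample size of 2430 stays as it is. If both sets must meet the margin there is some loss of power, expected to be small but not quantified here. This changes the analysis definition only and does not touch clinical management.
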